#### Follow up

The duration of follow-up for individual participants will vary. Every participant will be followed up with radiological assessments until disease progression or treatment discontinuation, whichever occurs later. Safety follow-up will continue for 100 days after the last dose of study drug or death, whichever occurs earlier. A follow-up visit will be conducted at 30 days post last dose of trial treatment where assessments will include: clinical assessment; adverse event reporting; FBC; U&Es; LFTs; TFTs; and cortisol. Participants will be followed up for overall survival 12 months post last patient randomised via centre follow-up.

### Outcomes

#### Primary endpoint

The primary endpoint is the proportion of participants experiencing a grade 3 or 4 adverse reaction within the initial 12 months of treatment as graded by CTCAE v5.0.

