## Methods

### Trial objectives

#### Primary objective

The primary aim of the PRISM trial is to assess whether the proposed alternative scheduling of ipilimumab (12-weekly), when given in combination with nivolumab, warrants further consideration based on safety and efficacy, as defined by the proportion of participants experiencing a grade 3 or 4 adverse reaction (AR) within 12 months and 12-month progression-free survival (PFS).

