#### Toxicity

We expect approximately 40% of participants to experience a grade 3 or 4 AR within the initial 12 months of treatment when treated with the standard schedule (Arm B) [18]. To detect a clinically relevant reduction to 22% with the modified schedule (Arm A) (equivalent to a 45% relative reduction; odds ratio (OR) = 0.423), with 80% power at the two-sided 10% significance level, would require 178 participants, allowing for 5% attrition.

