### Statistical methods and analysis

Analyses will be conducted following modified intention-to-treat principles (unless otherwise stated a priori) meaning participants will be analysed in the group to which they were randomised regardless of compliance or cross-over. Participants will be included in the primary and key secondary analyses provided they have received at least one dose of trial treatment and have provided the relevant outcome data.

The primary analysis will examine differences in the proportion of participants experiencing a grade 3 or 4 AR within the initial 12 months of treatment between trial arms using a logistic regression model, adjusting for minimisation factors (IMDC prognostic group, nephrectomy status, disease type); odds ratios will be presented alongside corresponding confidence intervals (CI). Pre-specified sensitivity analyses may be conducted as appropriate.

Should the primary analysis show a reduction in toxicity for the modified schedule (Arm A) compared with the standard schedule (Arm B), the formal key secondary analysis will be conducted. If the lower limit of the 90% CI for the proportion of participants alive and progression-free at 12 months in the modified schedule only (Arm A) excludes the rate of no interest based on historical (sunitinib-treated) control data (39.7%), the modified schedule will be deemed to have sufficient activity in line with that expected in the CM214 trial. The trial will provide supportive information rather than definitive conclusions of superiority of the modified arm to sunitinib.

Secondary endpoints will be analysed using summary statistics alongside confidence intervals where appropriate. All analyses will be fully detailed in a statistical analysis plan prior to being undertaken.

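### The primary toxicity endpoint stops at grade 4, so a fatal reaction with no grade 3 or 4 reaction also on record is not counted as toxicity

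*Protocol article*

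**What the plan says.** The Primary endpoint section states: "The primary endpoint is the proportion of participants experiencing a grade 3 or 4 adverse reaction within the initial 12 months of treatment", with CTCAE v5.0 as the grading scale. The same grade limit stands in four other places:

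- **Abstract (Methods)**: grade 3 or 4, within 12 months.
- **Primary objective**: "proportion of participants experiencing a grade 3 or 4 adverse reaction (AR) within 12 months".
- **Sample size, Toxicity**: "We expect approximately 40% of participants to experience a grade 3 or 4 AR within the initial 12 months of treatment", followed by a target of 22% in Arm A.
- **Statistical methods and analysis**: the logistic model will "examine differences in the proportion of participants experiencing a grade 3 or 4 AR within the initial 12 months of treatment between trial arms".

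No section mentions grade 5 or grade 3 and above, or says how a fatal reaction enters the primary outcome. The analysis set requires at least one dose and that participants "have provided the relevant outcome data". The formal test of 12-month PFS follows only if the primary analysis shows less toxicity in Arm A.

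**The concern.** On the scale that the protocol names, grade 5 is death from the event. An endpoint that stops at grade 4 measures severe toxicity but leaves out its worst form. Someone who dies of a reaction cannot record a grade 3 or 4 reaction afterwards, and the Follow up section ends safety follow-up at death. Unless a grade 3 or 4 reaction was recorded first, that participant never becomes an event.

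This is not a detail left open for the analysis plan. The article fixes the grades itself, in the same way, in five places, so an analysis plan that added grade 5 would be changing the stated primary endpoint. At stake is the toxicity comparison, which is both the primary result and the gate to the formal efficacy test.

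**Working it through.** **Inputs.** From the Toxicity section: 40% in Arm B, 22% in Arm A, two-sided 10% level, 80% power, 5% attrition, total 178. From Trial design and Sample size: 2:1 allocation, 189 recruited. Evaluable: 189 × 0.95 ≈ 180, that is 60 in Arm B and 120 in Arm A.

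**The plan's own figures.** Odds ratio: (0.22/0.78)/(0.40/0.60) = 0.423, as stated. Sample size by the pooled formula, with weighted mean rate p̄ = (0.40 + 2 × 0.22)/3 = 0.28:

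n_B = [1.645·√(p̄(1−p̄)·1.5) + 0.842·√(0.24 + 0.1716/2)]² / 0.18² = (0.9045 + 0.4804)² / 0.0324 ≈ 59.2, rounded up to 60.

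The total is 180 evaluable, and 180/0.95 ≈ 190 with attrition. The stated 178 is close to the number before attrition and is not reproduced as a number after it. This does not affect the point, because 189 are recruited and pooled power at 60/120 is 80.5%.

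**How a participant is scored under the stated definition.**

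| Reactions recorded within 12 months | Primary event? |
|---|---|
| Grade 3 or 4, not fatal | Yes |
| Grade 3 or 4, and a fatal (grade 5) reaction | Yes |
| Grade 5 only | No |

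Only the last row is lost. The second row would join it if the database kept a single worst grade per participant.

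**Size per case.** Arm A: 1/120 = 0.83 points. Arm B: 1/60 = 1.67 points. The article gives no rate of fatal reactions, so 1% to 3% fatal-only is an assumption, and probably a high one, because only part of all fatal reactions will be fatal-only. It corresponds to 1.2 to 3.6 participants in Arm A (120 × 0.01 to 0.03) and 0.6 to 1.8 in Arm B (60 × 0.01 to 0.03).

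**Effect at the decision boundary.** Unadjusted pooled test, z = (p_B − p_A)/√[p̄(1−p̄)(1/60 + 1/120)], with 24/60 events in Arm B:

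- Arm A 33/120: p̄ = 57/180, z = 1.70, two-sided p = 0.089, significant at 10%.
- Arm A 34/120: p̄ = 58/180, z = 1.58, two-sided p = 0.114, not significant.

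**Effect on the false-positive rate.** Suppose the true grade 3–5 rate is 40% in both arms. The chance of declaring Arm A less toxic on the grade 3–4 count is Φ[((p_B − p_A) − 1.645·SE₀)/SE₁], where SE₀ is the pooled and SE₁ the unpooled standard error and the rates exclude fatal-only cases.

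| Fatal-only, points | Arm A only | Both arms equally | Arm B only |
|---|---|---|---|
| 1 | 6.5% | 5.0% | 3.8% |
| 2 | 8.4% | 5.0% | 2.8% |
| 3 | 10.6% | 5.0% | 2.0% |

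**Power if grade 5 is counted.** Same formula, with the fatal-only rate added to 40% and 22%; it is 80.5% with none added.

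| Points added | Both arms | Arm A only | Arm B only |
|---|---|---|---|
| 1 | 79.8% | 76.1% | 83.8% |
| 2 | 79.2% | 71.2% | 86.7% |
| 3 | 78.7% | 66.0% | 89.2% |

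The fall in the Arm A column is not a cost of the better definition: in that case the true difference in severe toxicity is smaller than planned.

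**The case against.** The best defence has five parts.

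1. **Most fatal reactions may count anyway.** The endpoint counts anyone who experiences a grade 3 or 4 reaction, not those whose worst grade is 3 or 4, and adverse events are reported every 2 to 4 weeks. This stands. A reader might infer that every participant killed by a reaction is scored as free of severe toxicity; the wording does not support that.
2. **The direction is open.** A reader might infer that the omission always helps Arm A. It does so only if fatal-only cases are proportionally more frequent there. If they are more frequent in Arm B, the omission makes it harder for Arm A to pass; if balanced, the false-positive rate stays near 5%. This stands, and one event can tip any result at its boundary.
3. **The scoring is not certain.** Given the outcome-data condition, such a participant might be left out rather than scored as a non-event. This stands, but in neither case is the death counted as toxicity.
4. **Deaths are not hidden.** They are failures in PFS, they count in overall survival, and fatal reactions belong in the safety summaries, which the monitoring committee also oversees. The schedule must show promise on both tolerability and efficacy. This limits the harm, but none of it restores the event to the toxicity comparison: the safety summaries are descriptive, and the formal PFS test concerns Arm A alone, after the gate.
5. **Grade 3 or 4 matches the CheckMate 214 figure.** The article does quote a 46% grade 3 or 4 rate from that trial. The primary comparison, however, is randomised and internal and does not need the match; a descriptive line keeps it.

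A sensitivity analysis counting grades 3 to 5 would fit the article's general provision for such analyses, but the gate would still rest on the incomplete count.

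**Conclusion.** The point holds in limited form. As defined, the primary endpoint does not count a fatal reaction unless a grade 3 or 4 reaction was also recorded within 12 months. This is a stated rule that misclassifies, not a missing detail. Its expected numerical effect is small: 0.8 points per case in Arm A and 1.7 in Arm B, against an 18-point planned difference. It could decide the primary result only near the boundary or if cases cluster in one arm. The error rates above the nominal 5% (6.5% to 10.6%) require all fatal-only cases to fall in Arm A at an assumed 1% to 3%; the article supports neither the rate nor the imbalance. All calculations are unadjusted normal approximations with 60 and 120 evaluable participants, not the adjusted logistic model. The reason to act is that the definition leaves the worst toxicity out of the gating comparison and is cheap to correct.

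**What to change.** Define the event as at least one adverse reaction of grade 3 or higher (grades 3 to 5) within the initial 12 months of treatment. Use that definition in the Abstract, Primary objective, Toxicity sample size, Primary endpoint and Statistical methods sections, and for the outcome in the logistic model. Confirm that the 40% and 22% planning rates rest on a compatible definition. Report grade 3–4 alone as a descriptive line for comparison with CheckMate 214.

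The data are already collected, since reactions are graded by CTCAE v5.0. The cost is a small change to a primary endpoint while recruitment is open, with the text changed in five places, and a headline rate that no longer exactly matches the CheckMate 214 grade 3–4 figure. Holding 80% power with 1, 2 or 3 points added in both arms would take 193, 196 or 199 participants with attrition, against 190 by the same formula now; at the recruited 189 the loss of power is under 2 points.

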#### Key secondary endpoint

Efficacy forms a key secondary endpoint of the study and will be based on the proportion of participants alive and progression-free at 12 months. Progression-free survival will be calculated from the date of randomisation to first documented evidence of disease progression (based on RECIST v1.1 criteria) or death. This landmark survival endpoint provides a pragmatic and timely readout of efficacy in this phase II trial and was selected before the results of the CM214 trial were available. Since the CM214 trial has now reported, additional exploratory analyses will be considered (such as the presentation of summary statistics for PFS at 12 m by prognostic group) and will be pre-specified prior to the final analysis being conducted.

#### Secondary endpoints

*Safety and toxicity*: adverse reactions (ARs), serious adverse events (SAEs), serious adverse reactions (SARs) and suspected unexpected serious adverse reactions (SUSARs) as measured throughout the trial and graded by common terminology criteria for adverse events (CTCAE) v5.0;*Treatment tolerability*: the proportion of participants who experience a treatment delay, the average number of treatment delays per participant and the duration of delays as measured over the course of trial treatment;*Treatment discontinuation*: rates of treatment discontinuation at any point during trial treatment and reasons;*Overall response*: the proportion of participants with partial response or complete response (PR or CR) as their best response to treatment prior to first-progression as defined by RECIST v1.1;*Duration of response*: calculated from first observation of at least PR until disease progression (as defined by RECIST v1.1) or death;*Overall survival:* calculated from the date of randomisation to the date of death from any cause;*Response rate for treatment beyond progression:* the proportion of participants showing a partial or complete best response (PR or CR) as defined by RECIST v1.1 when treated beyond progression.*Health-related Quality of Life:* assessed using the FKSI-19; the EORTC QLQ-C30; study-specific symptoms and the EQ-5D-5L^TM^ and scored using the corresponding scoring manuals.

### Statistical methods and analysis

Analyses will be conducted following modified intention-to-treat principles (unless otherwise stated a priori) meaning participants will be analysed in the group to which they were randomised regardless of compliance or cross-over. Participants will be included in the primary and key secondary analyses provided they have received at least one dose of trial treatment and have provided the relevant outcome data.

The primary analysis will examine differences in the proportion of participants experiencing a grade 3 or 4 AR within the initial 12 months of treatment between trial arms using a logistic regression model, adjusting for minimisation factors (IMDC prognostic group, nephrectomy status, disease type); odds ratios will be presented alongside corresponding confidence intervals (CI). Pre-specified sensitivity analyses may be conducted as appropriate.

Should the primary analysis show a reduction in toxicity for the modified schedule (Arm A) compared with the standard schedule (Arm B), the formal key secondary analysis will be conducted. If the lower limit of the 90% CI for the proportion of participants alive and progression-free at 12 months in the modified schedule only (Arm A) excludes the rate of no interest based on historical (sunitinib-treated) control data (39.7%), the modified schedule will be deemed to have sufficient activity in line with that expected in the CM214 trial. The trial will provide supportive information rather than definitive conclusions of superiority of the modified arm to sunitinib.

Secondary endpoints will be analysed using summary statistics alongside confidence intervals where appropriate. All analyses will be fully detailed in a statistical analysis plan prior to being undertaken.

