### Randomisation

Randomisation will be performed following confirmation of eligibility (and prior to any trial treatment) via a central automated 24-h system (provided by University of Leeds) to either the modified schedule or the standard schedule on a 2:1 allocation ratio in favour of the modified schedule. A computer–generated minimisation programme incorporating a random element generated by the independent CTRU Statisticians will be used to ensure treatment groups are well balanced proportionately with respect to: IMDC prognostic group (favourable/intermediate/poor risk); nephrectomy status (nephrectomy/no nephrectomy); and disease type (metastatic/locally advanced). Irrespective of their randomised allocation, participants should commence therapy within 14 days of randomisation.

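### The Arm A 12-month PFS test, timed from randomisation and judged against a fixed 39.7%, is restricted to dosed participants with outcome data and so is open to bias in either direction

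*Protocol article*

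**What the plan says.** Statistical methods and analysis describes a modified intention-to-treat approach: participants stay in their randomised group whatever their compliance, but enter the primary and key secondary analyses only "provided they have received at least one dose of trial treatment and have provided the relevant outcome data". What counts as relevant outcome data is not defined.

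Under Key secondary endpoint, efficacy "will be based on the proportion of participants alive and progression-free at 12 months", and "Progression-free survival will be calculated from the date of randomisation to first documented evidence of disease progression" or death. Under Randomisation, "participants should commence therapy within 14 days of randomisation", so there is an interval in which a participant already counts for PFS but has not been dosed.

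The efficacy decision uses Arm A alone: the lower limit of a 90% CI must exclude 39.7%, a rate taken from sunitinib-treated historical controls. The test is run only if the primary analysis shows less toxicity. The Sample size section requires the modified schedule to show promise on both tolerability and efficacy before it goes further.

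**The concern.** Two groups leave the denominator.

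- **Not dosed.** Someone who progresses, deteriorates, dies or declines between randomisation and first dose is removed, although the PFS clock has started.
- **Lost before 12 months.** On the plain reading, someone lost without a recorded event has no 12-month status and is removed. Someone who progressed before being lost has a known status and stays in as a failure.

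Inclusion therefore depends partly on the outcome itself. In a two-arm comparison, similar selection in both arms could partly cancel. Here one arm is compared with a constant, so nothing offsets it. The result is half of the decision on whether the schedule merits further study, and two or three participants can settle it.

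**Working it through.** **Inputs (Protocol article, Sample size: Efficacy).** Sunitinib median PFS 9 months, exponential survival, hazard ratio 0.73, 120 evaluable in Arm A, one-sided 5%, 80% power, 2:1 randomisation, 189 recruited allowing for 5% attrition.

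**1. Reproduce the plan's figures.**
- Null rate: exp(-ln2 × 12/9) = 0.397. Target: 0.397^0.73 = 0.509.
- n = [1.645√(0.397 × 0.603) + 0.842√(0.509 × 0.491)]² / (0.509 - 0.397)² = 119.7, so 120.
- Total: 120 × 1.5 × 1.05 = 189, of whom 189 × 2/3 = 126 in Arm A.

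The sample size is not in error. It is a plain one-sample binomial size with no censoring term, inflated so that about 6 of 126 may drop out and 120 be analysed. That supports the complete-case reading but does not prove it.

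**2. Count needed to pass (lower 90% limit above 39.7%).** The article does not name the interval, so both common choices are shown.

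| Responders | Wald limit | Exact limit |
|---|---|---|
| 57/120 | 40.0% | 39.7% (does not exclude the stated 39.7%) |
| 58/120 | 40.8% | 40.5% |
| 57/126 | 37.9% | 37.7% |
| 58/126 | 38.7% | 38.5% |
| 59/126 | 39.5% | 39.2% |
| 60/126 | 40.3% | 40.0% |

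With 120 analysed, the pass mark is 57 (Wald) or 58 (exact). With all 126 it is 60 under either. If the six excluded are failures, 58 responders pass over 120 and fail over 126, whichever limit is used.

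**3. Selective exclusion.** Suppose the true rate over 126 is 39.7% and the six excluded have 12-month PFS rate q. The analysed rate is (126 × 0.3969 - 6q)/120, and type I error is the binomial tail at or above the pass mark. The documents give no loss pattern, so q is an assumption.

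| q | Analysed rate | Type I error, Wald (57 or more) | Type I error, exact (58 or more) |
|---|---|---|---|
| 0 (all failures) | 41.7% | 11.5% | 8.3% |
| 0.20 | 40.7% | 7.7% | 5.4% |
| 0.30 | 40.2% | 6.2% | 4.3% |
| 0.397 (same as the rest) | 39.7% | 5.0% | 3.4% |
| 1 (all progression-free) | 36.7% | 1.0% | 0.6% |

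Using the rounded 0.397 in place of 0.3969 moves the 8.3% to 8.4%.

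**4. Random loss.** Let a share c of participants have a dropout time uniform over 12 months, independent of outcome. Those whose event comes first stay in; the others drop out. The analysed rate is p(1 - c) / [(1 - c) + c·P(event before dropout)], where P(event before dropout) = 1 - (1 - p)/(-ln p).
- p = 0.397: this probability is 0.347, and the analysed rate is 39.0% (c = 5%) or 38.2% (c = 10%).
- p = 0.509: it is 0.273, and the analysed rate is 50.2% or 49.4%.

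The shift is 0.7 to 1.5 points downward, which costs power rather than type I error.

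**The case against.** The strongest reply is that the article does not fix the estimator. It defines PFS as a time to event, describes the 12-month figure as a landmark measure, derives its rates from exponential survival and defers full analysis detail to a SAP that is not shown. If any PFS follow-up counts as relevant outcome data and Kaplan-Meier is used, participants lost event-free contribute until censoring. This stands, and it limits confidence. It does not remove the dosing condition, which the article states outright.

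The magnitude can also be challenged. The 11.5% needs every excluded participant to be a failure and a Wald limit. A progression or death documented after the first dose counts as outcome data and stays in. Eligibility requires a life expectancy of at least 6 months and a Karnofsky score of at least 70%, dosing should follow within 14 days, and scans continue until progression or treatment discontinuation, whichever is later. Six undosed or unobserved failures are therefore an extreme, and that too stands.

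A reader might infer that the PFS estimate is certainly biased, or biased upward. The documents do not support this: they give no loss pattern, and the direction depends on who is lost. A reader might also infer that the primary toxicity analysis is compromised because the same rule covers it. No bias is shown there, and requiring one dose is ordinary for an adverse-reaction endpoint.

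Finally, the test is gated on the primary result and described as supportive. That lowers the severity, but it remains a formal pass/fail rule.

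**Conclusion.** The point holds for the key secondary endpoint only. The stated inclusion rule fits poorly with a PFS origin at randomisation and, read plainly, lets the outcome influence the denominator of a single-arm test against a constant. This is a risk of bias of unknown direction, not a demonstrated bias. At the planned attrition of 6 in 126, the analysed null rate could lie anywhere from 36.7% to 41.7%; both ends are extreme assumptions. Type I error in the upper extreme is 11.5% (Wald) or about 8.3% (exact), against 5.0% and 3.4% if those excluded match the rest. Milder selection (q of 0.20 to 0.30) gives 6.2-7.7% or 4.3-5.4%. A borderline pass can become a fail under either interval. Severity is moderate and confidence medium, since a SAP that specifies Kaplan-Meier and counts partial follow-up as outcome data would remove much of the concern, leaving the exclusion of undosed participants.

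**What to change.** For the key secondary endpoint, define the analysis population as all participants randomised to Arm A. Estimate 12-month PFS by Kaplan-Meier from randomisation, censoring at the last adequate disease assessment, and compare the lower limit of its 90% CI with 39.7%. Name the CI method in advance.

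Report two sensitivity analyses: the dosed, complete-case proportion, and a proportion over all 126 that counts unknown status as failure. The second matters because Kaplan-Meier assumes that censoring is uninformative, and because an undosed participant with no follow-up adds nothing to the estimate. Define relevant outcome data for each endpoint, and keep the dosed population for toxicity.

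The cost is protocol or SAP wording, settled before the final analysis. No new data items are needed, because the Follow up section already has every participant scanned until progression or treatment discontinuation. The downside is that the estimate may be slightly less favourable.

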## Abstract

**Background:**

The combination of nivolumab, a programmed death-1 (PD-1) targeted monoclonal antibody, with the cytotoxic T-lymphocyte antigen-4 (CTLA-4) targeted antibody, ipilimumab, represents a new standard of care in the first-line setting for patients with intermediate- and poor-risk metastatic renal cell carcinoma (mRCC) based on recent phase III data. Combining ipilimumab with nivolumab increases rates of grade 3 and 4 toxicity compared with nivolumab alone, and the optimal scheduling of these agents when used together remains unknown. The aim of the PRISM study is to assess whether less frequent dosing of ipilimumab (12-weekly versus 3-weekly), in combination with nivolumab, is associated with a favourable toxicity profile without adversely impacting efficacy.

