### Study rationale

Whilst CM214 has established the superior efficacy of combination nivolumab with ipilimumab over sunitinib in patients with intermediate- and poor-risk mRCC, optimal scheduling of these drugs has not been explored in this disease area. Additionally, improving our current understanding of why some patients respond to immunotherapy whilst many others derive no benefit is recognised as a research priority and translational studies focusing on predictive biomarkers forms a further important exploratory objective of the trial.

PRISM is a Phase II, open label, multi-centre, parallel group, randomised controlled trial. Our trial was designed before CM214 results were available and seeks to establish whether less frequent scheduling of ipilimumab is associated with improved tolerability in patients with mRCC in comparison to the schedule used in CM214, without adversely impacting activity (in comparison with historic control data).

Studies in other cancer types demonstrate ipilimumab dose and / or frequency can affect the toxicity and efficacy of treatment. In advanced melanoma, for example, 10 mg/kg ipilimumab every 3 weeks for 4 doses was associated with longer median OS but higher rates of grade 3 or 4 toxicity, in comparison to 3 mg/kg dosing [10]. A recently reported melanoma trial comparing I3 + N1 versus I1 + N3 again showed a favourable toxicity profile associated with a lower dose of ipilimumab, with no apparent difference in efficacy at a minimum follow-up of 12 months [11]. Varying doses and schedules of ipilimumab plus nivolumab have also been examined amongst 8 cohorts within the phase Ib CM012 study in patients with non-small cell lung cancer, including nivolumab 3 mg/kg q2W plus ipilimumab 1 mg/kg given either 6- (*n* = 39) or 12- (*n* = 38) weekly [12]. The schedule N3 (2-weekly) + I1 (6-weekly) was selected for phase III evaluation based on its safety and efficacy profile [13]. Thus, formal investigation of the scheduling of ipilimumab when given in combination with nivolumab in patients with mRCC is warranted.

It was not feasible to design the study for an internal comparison of efficacy given the phase II nature of the trial and the required sample size for such a comparison. As the trial was designed prior to CM214 results being available, PRISM is powered to compare activity of the modified schedule with historic sunitinib control data, however ancillary analyses will explore results in relation to CM214.

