#### Efficacy

Assuming exponential survival, a median progression-free survival (PFS) with sunitinib of 9 months [5], (equivalent to 39.7% patients progression-free at 12 months) and targeting a minimum clinically relevant hazard ratio of 0.73 (corresponding to a median PFS in the modified Arm A schedule of 12.3 months, or 50.9% progression-free at 12 months) 120 participants would be required in the modified schedule arm to give 80% power at the one-sided 5% significance level. With 2:1 randomisation, a total of 189 patients will need to be recruited to allow for 5% attrition. Comparison with historical control data is based on data available at the time of design from the COMPARZ study [5], however additional unpowered analyses will be considered in light of the CM214 results now being available.

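### A pass of the efficacy rule shows activity above historical sunitinib only, yet the plan words it as activity in line with CM214

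*Protocol article*

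**What the plan says.** Under Statistical methods and analysis, the formal key secondary analysis is run only if the primary analysis shows less toxicity in Arm A. It takes the 90% confidence interval for the proportion alive and progression-free at 12 months, in Arm A alone, and asks whether the lower limit lies above 39.7%. If so, "the modified schedule will be deemed to have sufficient activity in line with that expected in the CM214 trial". The sentence that follows describes the result as supportive rather than definitive, but only with regard to superiority over sunitinib.

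The Efficacy part of Sample size gives the source of the threshold. A median PFS of 9 months on sunitinib is "equivalent to 39.7% patients progression-free at 12 months". The design is "targeting a minimum clinically relevant hazard ratio of 0.73", which corresponds to "50.9% progression-free at 12 months", and "120 participants would be required in the modified schedule arm to give 80% power at the one-sided 5% significance level".

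Study rationale is open about the comparator: "PRISM is powered to compare activity of the modified schedule with historic sunitinib control data". The same section says that an internal efficacy comparison was not feasible, and the Discussion says the same of non-inferiority to the current standard. The Abstract describes the aim as finding out whether 12-weekly rather than 3-weekly ipilimumab "is associated with a favourable toxicity profile without adversely impacting efficacy".

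**The concern.** The test and the conclusion use different benchmarks. A lower limit above 39.7% is evidence that Arm A does better than a historical sunitinib rate. Activity in line with CM214 is a statement about the nivolumab plus 3-weekly ipilimumab combination. To support it, the rule would need a combination rate, an acceptable shortfall from that rate, or the randomised Arm B result. It has none of these.

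This matters because the sentence is a pre-specified decision statement. Under Sample size, the efficacy element is one of two that the schedule must meet to warrant further investigation. The Background calls the 3-weekly combination a new standard of care in intermediate- and poor-risk disease. A reader of the final report who sees activity described as in line with CM214 would take it that little has been lost against that standard, which the rule does not examine.

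**Working it through.** **Inputs.** From Sample size, Efficacy: sunitinib median PFS 9 months, p0 = 39.7%, target hazard ratio 0.73, p1 = 50.9%, one-sided 5%, 80% power, n = 120 in Arm A, 2:1 allocation. From Statistical methods and analysis: lower limit of a 90% interval, Arm A only. The article gives no 12-month PFS for CM214 or for the standard schedule, so any such rate below is an assumption and is shown as a range.

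**1. The plan's own figures reproduce.**
- Exponential conversion: 0.5^(12/9) = 0.397; 0.397^0.73 = 0.509; 9/0.73 = 12.3 months.
- One-sample size: n = [1.645·√(0.397·0.603) + 0.842·√(0.509·0.491)]² / (0.509 − 0.397)² = 119.7, rounded up to 120.

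The sample size is right for a test against sunitinib.

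**2. Smallest passing result with 120 evaluable.**
- 57/120 = 47.5%: Wald lower limit 0.475 − 1.645·√(0.475·0.525/120) = 0.475 − 0.075 = 0.400, which passes. The Wilson limit is 0.401, which also passes.
- 56/120 = 46.7%: Wald lower limit 0.467 − 0.075 = 0.392, which fails.
- With the exact (Clopper-Pearson) interval the first pass is 58/120 = 48.3%, lower limit 0.405.

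At 57/120 the implied hazard ratio against sunitinib is ln(0.475)/ln(0.397) = 0.81.

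**3. Chance of passing.** Binomial with n = 120 and 12-month status known for all; the efficacy rule taken alone, given that it is reached:

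| True 12-month PFS | P(at least 57) | P(at least 58) |
|---|---|---|
| 39.7% | 5.0% | 3.4% |
| 45.0% | 32.2% | 26.0% |
| 50.9% | 79.9% | 74.3% |

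**4. What a pass says about the standard schedule.** Let S be the assumed 12-month PFS on the standard schedule. A schedule that loses half the gain over sunitinib has true rate 0.397 + 0.5·(S − 0.397). The last column is (0.475 − 0.397)/(S − 0.397), the share of the gain kept at an observed 57/120.

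| Assumed S | Rate with half the gain lost | P(at least 57) | P(at least 58) | Share kept at 57/120 |
|---|---|---|---|---|
| 50% | 44.85% | 31.1% | 24.9% | 76% |
| 55% | 47.35% | 52.3% | 45.0% | 51% |
| 60% | 49.85% | 72.8% | 66.4% | 38% |

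The better the standard schedule is, the more loss the rule lets through, because the threshold stays at the sunitinib rate.

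**5. What the randomised comparison could show.** With 120 against 60 and both arms near 50.9%, the unadjusted 90% half-width for Arm A minus Arm B is 1.645·√[0.509·0.491·(1/120 + 1/60)] = 0.130, or 13 points. For scale, take a non-inferiority test at 2:1, one-sided 5%, 80% power, both arms at 50.9%, with a margin of 11.2 points (50.9 − 39.7). It needs (1.645 + 0.842)²·0.509·0.491·1.5/0.112² = 185 in Arm B, or 555 in total. This agrees with the article's statement that a formal comparison was out of reach.

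**The case against.** The strongest defence is that the limitation is disclosed. The article says that PRISM was designed before CM214 reported, that it is powered against sunitinib, and that neither an internal nor a non-inferiority comparison was feasible. All of that stands, so the lack of a powered comparison is not the fault. It does make the CM214 phrase harder to defend, since the rule announces what the article says it cannot test.

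A reader might go further and infer that the standard schedule and CM214 play no part in the efficacy assessment. The article does not support that. Study rationale and Efficacy foresee unpowered analyses in relation to CM214. Key secondary endpoint says that added exploratory analyses will be pre-specified. Secondary objectives cover response, its duration and survival in each arm. What is missing is any use of CM214 or Arm B in the formal criterion.

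A reader might also take the Abstract's aim as a promise about 3-weekly ipilimumab. Study rationale ties the same aim to historical control data, so the Abstract is better read as a shortened form of it.

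Nor do the figures show that benefit would be lost. The 50.9% is a target over sunitinib and not a combination rate. Passing at an observed value below the target is normal for a test with 80% power there. At a true 45% the rule fails about 68% of the time. If the standard rate were itself near 47.5%, a pass at that value would involve no loss.

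Finally, the phrase may reflect what was expected of CM214 at the design stage. No figure for that expectation is given, and the threshold would still be the sunitinib rate.

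**Conclusion.** The point holds as a fault in the conclusion attached to the rule. The test, the 39.7% threshold and the 120 patients in Arm A are sound for a comparison with historical sunitinib. They cannot support a statement about CM214, and the disclaimer beside the rule does not reach that statement.

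The rule passes from 47.5% (48.3% with an exact interval). Whether that would hide a material loss cannot be settled from the article: the chance of passing with half the gain lost runs from about 25% to 73% over assumed standard rates of 50% to 60% and the two passing thresholds. The fault does not depend on where in that range the truth lies, because no value of the standard rate enters the rule.

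**What to change.** 1. In Statistical methods and analysis, word the conclusion of a pass as: Arm A's 12-month PFS excludes the historical sunitinib rate of no interest. Delete the phrase that refers to CM214.
2. Beside the rule, report the randomised Arm A minus Arm B difference in 12-month PFS, adjusted for the minimisation factors, with its 90% confidence interval, labelled supportive and unpowered.
3. Make no statement about preserved activity relative to the standard schedule unless that interval is shown with it.

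The cost is a change of wording and one analysis of data that the trial already collects. The price is a weaker claim and a visibly wide interval, about ±13 points. No patients are added, and the test, threshold and sample size do not change. The wording should be settled before the final analysis.
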